#### Major protocol deviations

- ① Informed consent form (ICF) not obtained
- ② Violation of the inclusion/exclusion criteria
- ③ Concomitant treatment with prohibited drugs during the study period
- ④ Baseline and Visit 8 immunogenicity tests not done
- ⑤ Randomization errors

For subjects who are considered to have any major protocol deviations other than the above listed,

a blind meeting will be held prior to database (DB) lock in which a decision will be made on whether to exclude the subjects from the PPS based on comprehensive assessment of the impact of the deviations on the study.

### **7.3.2 General principles of statistics**

For continuous data, descriptive statistics (number of subjects, mean, SD, minimum, median, maximum) will be presented. For categorical data, frequency and percentage will be presented, and if necessary, 95% two-sided confidence interval (CI) will also be calculated.

### **7.3.3 Analysis of demographics and baseline characteristics**

In terms of demographics and baseline characteristics, mean, SD, minimum, and maximum will be presented by treatment group for continuous data; and frequency and percentage will be presented by treatment group for categorical data.

### **7.3.4 Safety analysis (Part A & Part B)**

Results from Part A and Part B will be presented by phase of study.

#### **7.3.4.1 Adverse events**

Summary descriptions will be provided as below for details of treatment emergent AEs (TEAEs).

Frequency, incidence, and number of events will be presented for solicited local and systemic AEs observed for 7 days (Day 0~Day 6) after each IP dosing, immediate AEs (anaphylaxis related) occurring within 30 minutes after each IP dosing, and unsolicited AEs occurring within 28 days after the last IP dosing. By treatment group, type of AEs will be classified by severity, causal relationship, outcome, etc., and frequency, incidence, and number of events will be presented by category.

Additionally, frequency, incidence, and number of events will be presented for SAEs and AESIs collected within 52 weeks after the 2nd dose of the IP.

All AEs except for solicited local and systemic AEs will be classified by system organ class and preferred term of Medical Dictionary for Regulatory Activities.

#### **7.3.4.2 Clinical laboratory tests**

For hematology/blood chemistry as part of clinical laboratory tests, descriptive statistics will be presented by item and by visit; and for each item, descriptive statistics will be presented for change from before the 1st dose of the IP (screening) at each visit post-dose.

For each clinical laboratory test (hematology/blood chemistry/urinalysis), subjects who had a shift from normal/not clinically significantly (NCS) abnormal findings before the 1st dose of the IP (screening) to clinically significantly (CS) abnormal findings post-dose of the IP at least once will be summarized as frequency and percentage.

#### **7.3.4.3 Vital signs**

Descriptive statistics will be presented by visit. In addition, descriptive statistics will also be presented for change from before the 1st dose of the IP (Visit 2, baseline) at each time point post-dose.

#### **7.3.4.4 Physical examination**

Based on the assessment of physical examination results at each visit versus before the 1st dose of the IP (Visit 2) by treatment group, frequency and percentage will be presented by treatment group for subjects who had a shift from normal/NCS abnormal findings pre-dose to CS abnormal findings post-dose of the IP at least once.

### **7.3.5 Immunogenicity analysis**

#### **7.3.5.1 Part A**

- (1) GMT and GMFR compared to the baseline(Visit 2) of antigen protein-specific antibodies as measured by ELISA at pre-dose (Visit 2), on Day 21 (Visit 5) after the 1st dose, and on Day 21 (Visit 8), Week 26 (Visit 10), and Week 52 (Visit 11) after the 2nd dose of the IP

GMT of antigen protein-specific antibodies as measured by ELISA at each time point post-dose versus pre-dose (Visit 2) will be calculated, and 95% two-sided CIs of GMT ratio post-dose versus pre-dose as well as GMFR will be presented by treatment group.

- (2) Proportion of subjects with seroconversion to antigen protein-specific antibodies as measured by ELISA at pre-dose (Visit 2), on Day 21 (Visit 5) after the 1st dose and on Day 21 (Visit 8), Week 26 (Visit 10), and Week 52 (Visit 11) after the 2nd dose of the IP (seroconversion rate [SCR])

Post-dose SCR to antigen protein-specific antibodies as measured by ELISA at each point as well as its 95% two-sided CI will be presented by treatment group.

- (3) GMT and GMFR compared to the baseline of neutralizing antibodies to SARS-CoV-2 as analyzed by Focus Reduction Neutralization Test (Wild-type SARS-CoV-2) at pre-dose (Visit 2), on Day 21 (Visit 5) after the 1st dose, and on Day 21 (Visit 8), Week 26 (Visit 10), and Week 52 (Visit 11) after the 2nd dose of the IP

GMT of neutralizing antibodies to SARS-CoV-2 as analyzed by Focus Reduction Neutralization Test (Wild-type SARS-CoV-2) at each time point post-dose versus pre-dose (Visit 2) will be calculated, and GMT ratio post-dose versus pre-dose as well as its 95% two-sided CI will be presented by treatment group.

- (4) Proportion of subjects with seroconversion to neutralizing antibodies to SARS-CoV-2 as analyzed by Focus Reduction Neutralization Test (Wild-type SARS-CoV-2) at pre-dose (Visit 2), on Day 21 (Visit 5) after the 1st dose and on Day 21 (Visit 8), Week 26 (Visit 10), and Week 52 (Visit 11) after the 2nd dose of the IP (seroconversion rate [SCR])

Post-dose SCR to neutralizing antibodies to SARS-CoV-2 as analyzed by Focus Reduction Neutralization Test (Wild-type SARS-CoV-2) at each point as well as its 95% two-sided CI will be presented by treatment group.

### **7.3.5.2 Part B**

- (1) GMT and GMFR compared to the baseline (Visit 2) of antigen protein-specific antibodies as measured by ELISA at pre-dose (Visit 2), on Day 21 (Visit 5) after the 1st dose, and on Day

21 (Visit 8), Week 26 (Visit 10), and Week 52 (Visit 11) after the 2nd dose of the IP

GMT of antigen protein-specific antibodies as measured by ELISA at each time point post-dose versus pre-dose (Visit 2) will be calculated, and 95% two-sided CIs of GMT ratio post-dose versus pre-dose as well as GMFR will be presented by treatment group.

- (2) Proportion of subjects with seroconversion to antigen protein-specific antibodies as measured by ELISA on Day 21 (Visit 5) after the 1st dose and on Day 21 (Visit 8), Week 26 (Visit 10), and Week 52 (Visit 11) after the 2nd dose of the IP (SCR)

Proportion of subjects with seroconversion to antigen protein-specific antibodies as measured by ELISA at each time point post-dose of the IP and its 95% two-sided CI will be presented by treatment group.

- (3) GMT and GMFR compared to the baseline of neutralizing antibodies to SARS-CoV-2 as analyzed by Focus Reduction Neutralization Test (Wild-type SARS-CoV-2) at pre-dose (Visit 2), on Day 21 (Visit 5) after the 1st dose, and on Day 21 (Visit 8), Week 26 (Visit 10), and Week 52 (Visit 11) after the 2nd dose of the IP

GMT of neutralizing antibodies to SARS-CoV-2 as analyzed by Focus Reduction Neutralization Test (Wild-type SARS-CoV-2) at pre-dose (Visit 2) and at each time point post-dose will be calculated, and post-dose to pre-dose ratio as well as its 95% two-sided CI will be presented by treatment group.

- (4) Proportion of subjects with seroconversion to neutralizing antibodies to SARS-CoV-2 as analyzed by Focus Reduction Neutralization Test (Wild-type SARS-CoV-2) at pre-dose (Visit 2), on Day 21 (Visit 5) after the 1st dose and on Day 21 (Visit 8), Week 26 (Visit 10), and Week 52 (Visit 11) after the 2nd dose of the IP (SCR)

Post-dose SCR to neutralizing antibodies to SARS-CoV-2 as analyzed by Focus Reduction Neutralization Test (Wild-type SARS-CoV-2) at each point as well as its 95% two-sided CI will be presented by treatment group.

### **7.3.5.3 Exploratory assessment (Part A & B)**

- (1) T cell immune response markers as analyzed by Ex vivo IFN $\gamma$  and IL-4 ELISpot at pre-dose and (Visit 2) on Day 21 (Visit 5) after the 1st dose, and on Day 21 (Visit 8) after the 2nd dose of the IP

For T cell immune response markers as analyzed by Ex vivo IFN $\gamma$  ELISpot at pre-dose (Visit 2) on Day 21 (Visit 5) after the 1st dose, and on Day 21 (Visit 8) after the 2nd dose of the IP, number of subjects, mean, SD, median, minimum, and maximum will be presented, and change from pre-dose on Day 21 after the 1st and 2nd dose of the IP as well as its 95% two-sided CI will be presented by treatment group.

### **7.3.6 Handling of drop-outs or missing data**

In this study, imputation will not be applied to missing data.

### **7.3.7 Planned interim analysis and safety monitoring**

Upon completion of data collection from all subjects in Part A up to Day 28 after the 2nd dose of the IP (end of main study, Visit 9), DB lock will be carried out for a data analysis based on which interim study results will be presented.

Also, upon completion of data collection from all subjects in Part A up to Week 26 after the 2nd dose of the IP (Visit 10), DB lock will be carried out on those collected data and the interim study results will be presented.

The data from all subjects in Part B up to Day 28 (end of main study, Visit 9) will be collected and DB lock on these data will be carried out for a data analysis. The interim study results will be presented.

Subsequently, once all subjects in Part A and Part B complete the study (end of follow-up, Visit 11), DB lock will be carried out, and the final results will be presented.

For the purpose of safety monitoring, the principal investigator will serve as the protocol safety manager based on the level of risk involved in this study. During the study period, the principal investigator will monitor according to the protocol the safety of subjects participating in the study at the applicable institution.

Whenever an SAE and/or an ADR occurs, the principal investigator will collect and review the data of the relevant subject as well as relevant safety information. In the event of an AE, unexpected issue, or a protocol non-compliance, the principal investigator will report to the sponsor (including the CRO), the IRB, and if necessary, the Ministry of Food and Drug Safety (MFDS) according to the protocol, the IRB-specific regulations, Good Clinical Practice (GCP), and other applicable regulations. In addition, if efficacy and safety information that might have a significant impact on the continuation of the study according to Section 9.11. 'Early termination or suspension of the study' in the protocol becomes known, the principal investigator will report to the sponsor in a timely manner, and in turn, the sponsor will discuss and decide on study continuation according to the sponsor's SOP.

### **7.3.8 Data and safety monitoring board**

To review study data, the DSMB will be established by the sponsor. Members of the DSMB should ensure the integrity of the study and should not be affected by any factor except when necessary to maintain the safety of study subjects. Individuals who clearly have the financial or intellectual ownership of the IP or applicable procedures or any related conflicts of interest cannot be the members of the DSMB. The DSMB consists of a total of 4 individuals: 3 DSMB members including a chair and 1 administrative secretary. Of those, the 3 DSMB members will have the right to vote: 2 infectiology specialists and 1 statistician. The DSMB administrative secretary will perform administrative tasks for the operation of the DSMB and will not have the voting right. For detailed procedures and information, see 'The Charter of Data and Safety Monitoring Board'.

To determine dose escalation and enrollment status of remaining subjects in each low and high dose group in Part A, 'solicited/unsolicited AEs collected for 7 days after the IP' in the first 5 subjects in the low dose group will be assessed after the end of their Day 7 Visit following the 1st dose of the IP, based on which enrollment of the rest of subjects to the low dose group as well as enrollment to the high dose group will be determined.

In addition, upon the end of Day 28 Visit after the 2nd dose of the IP in the last subject in Part A, 'solicited/unsolicited AEs collected for 28 days after the 2nd dose of the IP' and other safety data obtained from all subjects in Part A will be assessed, verified, and analyzed by the DSMB. The DSMB members will review the adverse events of Part A subjects and assess where those AEs are considered as the criteria for discontinuation of the study. The relation between AE and IP will

also be analyzed and whether to proceed to Part B will be determined.

If DSMB meeting is necessary for review of ADR and confirmation of Enhanced disease in the event of Adverse Event of Special Interest (AESI), DSMB members may analyze the relationship between occurred AESI and IP and confirm whether AESI is Enhanced disease or not.

In the event of AEs that meet the 'criteria for study suspension' during the course of Part A and Part B, the DSMB will meet to assess the safety data and decide on study continuation. However, the placebo group is not subject to review by the DSMB.

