##### 3.1.1 Part A

Part A consists of two dose levels (low dose, high dose) of EuCorVac-19. Each dose group consists of 15 subjects in test group and 10 subjects in placebo group.

The first 5 subjects will be randomized and enrolled to the low dose group (Sentinel group: 3 subjects in Test group, 2 subjects in Placebo group); once the safety of the IP is confirmed in these subjects over 7 days after the 1st dose of the IP, the study will proceed to enroll the rest of 20 subjects to the low dose group. The rest of 20 subjects will be randomized to 12 subjects in Test group and 8 subjects in Placebo group. Also, the first 5 subjects will be randomized and enrolled

to the high dose group (Sentinel group: 3 subjects in Test group, 2 subjects in Placebo group); If no Grade  $\geq 3$  adverse drug reactions (ADRs) are reported within 7 days (Day 0 ~ Day 6) after the 1st dose of the IP, the rest of 20 subjects to the high dose group will be enrolled. The 20 subjects in the high dose group will be randomized to 12 subjects in Test group and 8 subjects in Placebo group.

If Grade  $\geq 3$  ADRs are reported within 7 days after the 1st dose of the IP in any of the first 5 subjects (Sentinel group) in each dose groups, the Data and Safety Monitoring Board (DSMB) will review the safety of the IP and determine whether to continue the study. If applicable, subject enrollment will be stopped and additional dosing in the existing subjects suspended until the decision is made on study continuation.

Once the safety results up to 28 days after the 2nd dose are collected from all subjects in Part A, the DSMB will review the safety data from all subjects enrolled in the high and low dose groups in Part A. The DSMB will assess if the event of ADRs in all subjects meet the criteria for study suspension and figure out the relationship between ADR and IP, based on which proceeding to Part B will be decided.

An interim analysis will be conducted using the immunogenicity data collected up to 21 days after the 2nd dose and the safety data collected up to 28 days after the 2nd dose in all subjects enrolled in Part A. Additional interim analysis will be performed using the safety and immunogenicity data collected up to 26 weeks after the 2nd dose in all subjects enrolled in Part A.

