## 5.5 Criteria for study suspension

During the study period, subjects will be monitored for the following ADRs that serve as criteria for study suspension. In the event of ADRs that are the criteria for study suspension, additional enrollment and treatment will be stopped at this time, and the DSMB will meet to decide study continuation.

- 1) Part A study: Grade  $\geq 3$  ADRs occurring within 7 days after the 1st dose in the first 5 subjects
- 2) Part A and Part B studies:
  - ① Grade  $\geq 3$  ADRs occurring within 3 days (Day 0 ~ Day 2) from the respective dosing day and lasting for  $> 1$  day despite active intervention for resolution in  $\geq 15\%$  of all

subjects planned to be enrolled to each study group (Part A:  $\geq 8/50$  subjects, Part B:  $\geq 35/230$  subjects)

- ② SADRs or Grade  $\geq 4$  ADRs occurring within 28 days after the respective dose of the IP

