#### **6.5 Maintaining and breaking the blind**

Part B is an observer-blind study. To maintain the quality of blinding, unblinded personnel belonging to the institution (person in charge of preparation for IP administration, person in charge of IP administration, pharmacist, CRA) will be designated. The unblinded personnel should perform only pre-defined tasks related to the study. In addition, a separate unblinded CRA will check the quantity and dispensing of the IP at the institution. The responsible unblinded CRA should perform only pre-defined tasks related to the study such as pharmacy monitoring and manufacturing and administration monitoring and should document the independent tasks. As a result, other investigators and sub-investigators, except for the unblinded personnel, will remain

blinded during the study period. The unblinded personnel in charge of preparation for IP administration and in charge of IP administration will prepare the IP in a place where the subject is not present and ask the subject to turn away at the time of IP administration so that the subject remains blinded during IP administration.

Allocation of unique codes by group will be managed by IWRS at the central enrollment center. In principle, randomization codes must remain blinded until the data lock for the analysis of the main study until the end of study and completion of analyses by the central laboratory so that assignment of each subject to relevant treatment group remains blinded. See Section 7.3.7 in this protocol for maintaining the blind during interim analysis.

If it is necessary to access a code during the study due to an SADR or the sponsor decides it is essential to access the code for the safety and right of the subject, the double blind may be broken, and blinding will be managed to ensure that only the unique code of the relevant subject is accessed.

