## 7. Statistical considerations

### 7.1 Sample size and rationale for sample size calculation

#### 7.1.1 Sample size

##### 7.1.1.1 Part A

To obtain 25 subjects per dose group who have at least one dose of the IP after randomization, at least 50 eligible volunteers based on the inclusion/exclusion criteria will be enrolled.

|                                                | Low dose group | High dose group |
|------------------------------------------------|----------------|-----------------|
| Number of subjects in test group               | 15 subjects    | 15 subjects     |
| Number of subjects in placebo comparator group | 10 subjects    | 10 subjects     |
| Total number of subjects                       | 25 subjects    | 25 subjects     |

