### 8.3.2 Assessment of causal relationship

In the event of an AE, association with the IP will be assessed by the investigator according to 2-

level criteria: 'related' or 'not-related'.

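### The 15% suspension count is set over all subjects, placebo included, but Section 7.3.8 takes the placebo group out of DSMB review at the meetings that count triggers

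*Protocol*

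**What the plan says.** **The criterion.** Section 5.5 stops enrolment and dosing, and calls the DSMB, when a certain kind of Grade 3 or higher reaction reaches 15%. The reaction must start within three days of a dose and last more than a day despite treatment. The base is all "subjects planned to be enrolled to each study group", and the bracketed counts (8/50 for Part A, 35/230 for Part B) show that the group meant is the whole Part, not an arm.

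**Who is in those totals.** Section 3.1.1 states for Part A: "Each dose group consists of 15 subjects in test group and 10 subjects in placebo group". With two dose groups, that is 30 vaccinees and 20 placebo subjects. Section 3.1.2 gives Part B as 100 low dose, 100 high dose and 30 placebo.

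**What the DSMB looks at.** Section 7.3.8 describes the meeting called when a suspension criterion is met. The text on that meeting ends: "decide on study continuation. However, the placebo group is not subject to review by the DSMB". Earlier in the same section, the scheduled review at the end of Part A covers all Part A subjects. Section 3.1.1 agrees: "The DSMB will assess if the event of ADRs in all subjects meet the criteria for study suspension".

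**Who judges relatedness.** Section 8.3.2 on causal relationship says that "association with the IP will be assessed by the investigator". Under Section 6.5, "other investigators and sub-investigators, except for the unblinded personnel, will remain" blinded.

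**The concern.** The trigger and the review are defined on different populations. The trigger's base includes placebo subjects, while the review it leads to leaves them out. The protocol also does not state whether a reaction in a placebo recipient counts toward the 8 or the 35.

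At a suspension meeting the DSMB has to judge whether the reactions are due to the vaccine. In a first-in-human trial the concurrent placebo arm is the most direct evidence on that. Without its cases and a by-arm comparison, background events that blinded investigators recorded as related are harder to separate from a true vaccine excess. The study could then be stopped needlessly, or dosing resumed wrongly.

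If placebo reactions are not meant to count, the problem is different. The threshold is described as 15%, but for the people who can contribute events it is higher.

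**Working it through.** **Inputs.** The 15% rule and the counts 8/50 and 35/230 come from Section 5.5. Part A has 15 + 15 = 30 vaccinees and 10 + 10 = 20 placebo subjects (3.1.1). Part B has 100 + 100 = 200 vaccinees and 30 placebo subjects (3.1.2).

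**Step 1. Reproduce the stated counts.** Take 15% of the base and round up.

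| Base | Part A | Part B |
|---|---|---|
| All planned subjects | 0.15 × 50 = 7.5 → 8 | 0.15 × 230 = 34.5 → 35 |
| Vaccinees only | 0.15 × 30 = 4.5 → 5 | 0.15 × 200 = 30 → 30 |

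The protocol's 8 and 35 match only when placebo is in the base. Placebo is 20/50 = 40.0% of it in Part A and 30/230 = 13.0% in Part B.

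**Step 2. If placebo reactions count.** Three parts of the protocol point this way: the reference in 3.1.1 to reactions in all subjects, blinded causality assessment, and Section 7.1.1.1, which counts placebo subjects among those given the IP ("To obtain 25 subjects per dose group who have at least one dose of the IP after randomization"). Some triggering cases can then be placebo cases. The protocol gives no expected rates, so the number is an assumption. It could be none. If rates were equal in all arms, the expected number would be 8 × 20/50 = 3.2 of 8 in Part A and 35 × 30/230 = 4.6 of 35 in Part B. Under 7.3.8 these cases fall outside the DSMB's review.

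**Step 3. If placebo reactions do not count.** Only vaccinees can reach the stated counts, so the working thresholds at full enrolment are 8/30 = 26.7% and 35/200 = 17.5%. The table gives the binomial chance of reaching the threshold, with the vaccinee rate of qualifying reactions assumed.

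| Assumed rate | Part A: 8 of 30 | Part A: 5 of 30 | Part B: 35 of 200 | Part B: 30 of 200 |
|---|---|---|---|---|
| 15% | 0.07 | 0.48 | 0.19 | 0.53 |
| 20% | 0.24 | 0.75 | 0.83 | 0.97 |
| 25% | 0.49 | 0.90 | 1.00 | 1.00 |
| 30% | 0.72 | 0.97 | 1.00 | 1.00 |

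On this reading the stated Part A count is much less sensitive than a true 15% rule across the whole range. In Part B the loss is clear at 15%, smaller at 20%, and gone by 25%.

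**Step 4. Compare the two readings.** Neither repairs the text. On the first, the review omits part of the trigger. On the second, the counts do not express the stated percentage and the DSMB still lacks the placebo comparison.

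**The case against.** **The sentence may be narrower than it looks.** It follows directly on events that meet a suspension criterion, so it could mean that placebo events do not by themselves call for a DSMB decision, not that the DSMB may never see placebo data. That is possible. A reader might infer a general bar, but the documents do not support one: the end-of-Part-A review covers all subjects, and the charter, to which 7.3.8 refers for detail, is not shown. On the narrower meaning, however, placebo events are outside the count and the thresholds in Step 3 follow.

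**Use of the term IP is mixed.** Section 8.1 defines an ADR by its relation to the IP, and Section 6.2 names the IP and placebo separately, whereas 7.1.1.1 treats placebo recipients as having had the IP. So it cannot be claimed outright that placebo reactions count. Blinded causality assessment favours counting them but does not settle it.

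**The DSMB would not be wholly in the dark.** A reader might infer that without placebo review it could not tell an even spread of reactions from one confined to vaccinees. That goes too far. If the pooled total that triggered the meeting is known, say 35, and the vaccinee cases are shown, subtraction gives the number of placebo cases. It would also still have the low and high dose groups, 100 each in Part B. What it lacks is the placebo cases themselves (timing, nature, severity, duration) and a proper by-arm table.

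**Scope is limited.** The pause under 5.5 is automatic, and entry to Part B rests on a review of all Part A subjects. Both points stand.

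**Conclusion.** The point holds with moderate confidence and should be fixed. The suspension criterion counts over a population that includes placebo (40.0% of the base in Part A, 13.0% in Part B), and the protocol then removes placebo from DSMB review at the meetings called on it. If placebo reactions count, the continuation decision is made without some of the triggering cases and without a by-arm placebo comparison. If they do not, the 15% rule is in effect 26.7% and 17.5% of vaccinees.

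The consequence lies in the continuation decision, mainly in Part B. Neither the automatic pause nor the scheduled end-of-Part-A review is affected.

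A reader might also conclude that a vaccinee-only rule should simply be written as 8/30 and 35/200. The protocol does not support that: 5.5 states 15%, and those counts would relax it.

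The enrolment figures and thresholds are the protocol's own. The placebo shares in Step 2 assume equal rates, and the probabilities in Step 3 assume vaccinee rates of 15% to 30%, full enrolment and no counted placebo events. The unseen charter could clarify intent, but it should not have to override an explicit protocol sentence.

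**What to change.** 1. **Section 7.3.8:** delete the sentence excluding the placebo group. State that at suspension-triggered meetings the DSMB receives safety tables by arm, placebo included, made by an unblinded preparer and circulated only to the DSMB. Align the charter.
2. **Section 5.5:** state that qualifying reactions in any subject, placebo included, count toward 8/50 and 35/230. These counts then stay as they are, and blinded staff can keep the pooled tally.
3. **Only if a vaccinee-only count is intended:** restate the thresholds at 15% of vaccinees, at least 5/30 in Part A and 30/200 in Part B. Keeping that tally would need unblinded staff.

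The cost of items 1 and 2 is wording in two sections and the charter, one placebo column in the DSMB tables, and an unblinded preparer. No new data are needed. As a protocol amendment the change needs IRB approval and, if necessary, regulator approval under Section 9.2.
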